#### **13.4.1. Analysis of the Primary Endpoint**

The number of events is based on the specific primary hypothesis that the overall survival rate of Arm 1 is higher than that of Arm 2. The results from D'Amico's paper with a similar patient group showed an 8-year overall survival rate of 61% in patients treated with RT only. Based on this result, we assume the control arm (i.e., Arm 2) will have an 8-year overall survival rate of 60%, which translates to a yearly hazard rate of 0.0639. The study is designed to show an absolute improvement of 7% in the 8-year overall survival rate in Arm 1 (i.e., an 8-year overall survival rate of 67%), which translates to a yearly hazard rate of 0.0501. Assuming an exponential distribution for overall survival, 716 deaths are required to detect a 21.6% relative reduction in the yearly death rate with 90% statistical power using a one-sided log-rank test at the 0.025 significance level.

A final analysis will be performed when 716 deaths occur. The time to overall survival will be measured from the date of randomization to the date of the death due to any cause (see section 11.3.10). We assume that the distribution of overall survival for each arm is an exponential distribution. We want to show that the hazard rate of Arm 1 ( $\lambda_1$ ) will be lower than that of Arm 2 ( $\lambda_2$ ) in the overall survival distribution. The following hypotheses are tested.

$$H_0: \lambda_2 \leq \lambda_1 \quad \text{vs.} \quad H_A: \lambda_2 > \lambda_1$$

The survival distribution of overall survival will be estimated by the Kaplan-Meier method. This hypothesis will be tested using a log-rank test statistic at a significance level  $\alpha = 0.025$ . In addition, the Cox regression model will be used to compare the treatment differences. Both unadjusted and adjusted hazard ratios and their respective 95% confidence interval will be computed. At least the treatment arm, the stratification variables (PSA, grade, and nodal status), age, and race (as appropriate) will be adjusted for in this analysis.

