### Cause of Death

| RTOG Protocol              | Median FU Years* | Gleason Groups** | Total Deaths | Prostate No. (%) | Other No. (%) | Unknown No. (%) |
|----------------------------|------------------|------------------|--------------|------------------|---------------|-----------------|
| 7706
(T1/T2)            | 9.75             | combined         | 258          | 76(29%)          | 165(64%)      | 17(7%)          |
|                            | 10.23            | 2-6              | 186          | 49(26%)          | 123(66%)      | 14(8%)          |
|                            | 7.69             | 7-10             | 62           | 25(40%)          | 34(55%)       | 3(5%)           |
| 8531+8610
(T3, RT only) | 4.51             | combined         | 159          | 75(47%)          | 73(46%)       | 11(7%)          |
|                            | 4.93             | 2-6              | 27           | 8(30%)           | 18(67%)       | 1(3%)           |
|                            | 4.44             | 7-10             | 127          | 67(53%)          | 52(41%)       | 8(6%)           |

\* for all eligible patients in the study

\*\* centrally reviewed

- The positive prostate study RTOG 85-31 showed that adjuvant hormonal arm is significantly better than the control arm in all disease related endpoints such as local control and disease free survival. However, survival benefit was only demonstrated in a group of patients with centrally reviewed Gleason scores 8-10.

One implication of these findings, which will be illustrated further later, is that a significant difference in absolute survival may be practically unattainable unless the treatment effect in disease specific survival is large. With this new information, the RTOG statistical unit felt that the protocol should be amended to incorporate these findings. In general, if neoadjuvant TAS is successful, there should be positive impact on disease specific survival. Thus, we modified the study to use disease specific survival as the primary endpoint with a median of 10 years follow-up, while the overall survival is considered as a secondary endpoint for the study. We also acknowledge that Gleason score is a significant risk factor and must be included in the design.

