## 13.7 Study Endpoints (7/1/97) (7/14/08)

The primary endpoint for this trial is overall survival, on which the sample size is calculated (See Section 11.3.10 for the definition). The absolute survival with failure of death from all

15

causes is a secondary endpoint. We also consider the time to second PSA failure defined in Section 11.3.7 as a secondary endpoint for the trial. The collection of these data allows us to examine the hypothesis that the second PSA failure is a surrogate for death from prostate cancer. With an adequate long period of follow-up, we should be able to study the relationship among these times to endpoints.

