## Estimated Hazard reduction in RTOG 8531

|                                 | Gleason
2-6 | Gleason
7-10 |
|---------------------------------|----------------|-----------------|
| Overall
survival             | 8%             | 32%             |
| Disease
specific
survival | NA             | 48%             |

We realize that because of the nodal involvement criteria of RTOG 8531, the selected sub-population includes less favorable patients than those in RTOG 94-08. Regardless of Gleason score groups, we would expect a hazard reduction in death from prostate cancer due to neoadjuvant hormone regimen to be less than 50%. Thus, we hypothesized a 33% hazard reduction in death from prostate cancer due to hormone treatment.

Based on the estimates of RTOG 77-06 given in assumption 1, we can translate the hazard reduction in disease specific survival into the hazard reduction in absolute survival. A 33% reduction in death from prostate cancer corresponds to an average of 11% reduction in death from all causes.

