### 13.8.2 Sample Size

For the primary endpoint, disease specific survival, we will use a two-sided log-rank test to detect the treatment effect of 33% reduction in hazard of death from prostate cancer with a significance level of 0.05 and a power of 90%. Using Lakatos' method (*assuming there is no drop-in and noncompliance, and loss of follow-up rate equals to the other cause mortality rate*), a total of 1779 patients is required to be accrued uniformly over five years and followed for additional eight years before the final analysis. Accounting for possible 10% unevaluable cases, **the total required sample size is 1980 for both arms of the study.**

With the proposed sample size, we will be able to detect a 16.7% average reduction in hazard of death from all causes with 75% power. (*However, if the reduction in death from all causes is 11%, a formidably large sample size will be required*).

If the current percentage (36%) of patients with Gleason 7-10 holds for the study, we will expect to enter 640 such evaluable patients. With this expected number of patients, we will be able to detect a 40% reduction in hazard of death from prostate cancer for patients with Gleason 7-10 with a statistical power of 80%. On the other hand, we will be able to detect a 20% reduction in hazard of absolute survival with statistical power of 53% for patients with Gleason 7-10.

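### Overall survival is powered at 90% for an underived 21.6% reduction in deaths, larger than section 13.8.1 expects; at the protocol's own 11%, 716 deaths give about 34% power

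*Protocol*

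**What the plan says.** Section 13.4.1, added when overall survival became the primary endpoint in 2008, gives the control arm an "8-year overall survival rate of 60%, which translates to a yearly hazard rate of 0.0639" and Arm 1 "an 8-year overall survival rate of 67%), which translates to a yearly hazard rate of 0.0501". From these it concludes that "716 deaths are required to detect a 21.6% relative reduction in the yearly death rate with 90% statistical power", using a one-sided log-rank test at 0.025. The final analysis is to be done at 716 deaths. The control rate is taken from a cited randomised trial; no source or reasoning is given for the 7-point gain.

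The 1997 planning text still stands in the same chapter:

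- Section 13.6, on the cause-of-death data, warns that "a significant difference in absolute survival may be practically unattainable unless the treatment effect in disease specific survival is large".
- Section 13.8.1 says that "we would expect a hazard reduction in death from prostate cancer due to neoadjuvant hormone regimen to be less than 50" per cent, hypothesises 33%, and adds that "A 33% reduction in death from prostate cancer corresponds to an average of 11% reduction in death from all causes".
- Section 13.8.2 sizes the trial at 1779 evaluable patients (1980 in total) for disease-specific survival, with five years of accrual and eight of follow-up. It adds that "we will be able to detect a 16.7% average reduction in hazard of death from all causes with 75% power", and that an 11% effect would need a very large trial.

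Section 13.7, to which section 13.3 sends the reader for the figure of 1980, says: "The primary endpoint for this trial is overall survival, on which the sample size is calculated". Its next sentence makes death from all causes a secondary endpoint.

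**The concern.** One chapter holds two incompatible views of how far the treatment can lower all-cause mortality. The 2008 power statement uses the larger effect and does not mention the smaller one. A reader of section 13.4.1 alone would think the trial is 90% sure to detect the benefit it was planned around. A reader of section 13.8 would expect an effect about half that size.

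This matters for interpretation. If androgen suppression works as section 13.8.1 hypothesises, a non-significant overall survival result is more likely than a significant one, yet with 90% power on the page it would readily be taken as evidence of no benefit. The endpoint wording in section 13.7 adds to the confusion, because it hides the fact that 1980 patients and 716 deaths come from two different calculations on two different endpoints.

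**Working it through.** **Inputs.** From 13.4.1: 8-year survival 60% and 67%, one-sided 0.025, 716 deaths. From 13.8.1: 33% cause-specific and 11% all-cause reduction, and the expectation of less than 50%. From 13.8.2: 1779 patients, 5 + 8 years, 16.7%, 75% power, two-sided 0.05. From the 13.6 table for RTOG 77-06: 76 of 258 deaths (29%) due to prostate cancer. Assumed: 1:1 allocation (the ratio is not stated), exponential survival and no loss to follow-up.

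**1. The plan's own figure.** Hazards are −ln(0.60)/8 = 0.0639 and −ln(0.67)/8 = 0.0501, so HR = 0.784, a 21.6% reduction. Deaths for 90% power:

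- Freedman: (1.960 + 1.282)² × [(1 + 0.784)/(1 − 0.784)]² = 717.
- Schoenfeld: 4 × (1.960 + 1.282)² / (ln 0.784)² = 710.

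The stated 716 is reproduced.

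**2. Translating between the two effects.** If only prostate-cancer deaths are affected, the all-cause reduction equals the cause-specific reduction times the prostate-cancer share of deaths. The protocol's ratio gives a share of 11/33 = 1/3.

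- A 50% cause-specific reduction gives 0.50 × 1/3 = 16.7% overall.
- A 21.6% overall reduction needs 0.216 / (1/3) = 65%.
- With the 29% share it needs 0.216 / 0.29 = 74%.

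Both needed values lie above the expected limit of 50%.

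**3. Power at 716 deaths.** Power = Φ(½√716 × |ln HR| − 1.96), with ½√716 = 13.38.

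| All-cause reduction | HR | Power |
|---|---|---|
| 21.6% | 0.784 | 90% |
| 16.7% | 0.833 | 69% |
| 11% | 0.89 | 34% |

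For 90% power at HR 0.89, Schoenfeld's formula gives about 3,095 deaths, more than the 1980 patients. The result is significant only if the observed HR is below exp(−1.96/13.38) = 0.864, so an observed reduction of exactly 11% would not be significant.

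**4. The 75% in 13.8.2.** That section gives no death count, so I derived one. With uniform accrual over A = 5 years and follow-up of F = 8, the proportion dying at hazard λ is 1 − [exp(−λF) − exp(−λ(A + F))]/(λA). For λ = 0.0639 this is 0.487; for λ = 0.0639 × 0.833 it is 0.426. Expected deaths are 1779/2 × (0.487 + 0.426) ≈ 812, and power at HR 0.833 is 74%. Control hazards from 0.055 to 0.070 give 727 to 866 deaths and 69% to 77% power. So the 75% is sound for its own design. It needs about 832 deaths, however, and the final analysis is now fixed at 716, where power is 69%.

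**5. Section 13.7 beside section 13.8.2.** Section 13.7 says overall survival is the basis of the sample size; 13.8.2 derives 1779 and 1980 from a 33% reduction in prostate-cancer death. Section 13.7 also makes overall survival primary in one sentence and all-cause death secondary in the next. These statements cannot both stand.

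**The case against.** The best defence is that section 13.8.1 states expectations, not limits. They rest on RTOG 77-06 and on a subset of RTOG 85-31 with 33 and 76 patients. The 1:3 ratio is an average: the same section puts all-cause mortality at 3 to 4 times prostate-cancer mortality for Gleason 2-6 but only about twice for Gleason 7-10. At a share of one half, 21.6% would need a 43% cut in prostate-cancer deaths, inside the expected range. The RTOG 85-31 table shows a 32% overall survival reduction for Gleason 7-10. Section 13.3 concedes that attributing deaths to prostate cancer is difficult, and section 13.4.1 is eleven years newer and cites a later trial.

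Much of this stands. A reader might infer that the protocol's figures rule out 21.6%; they do not. But the objection does not supply the missing derivation. Gleason 7-10 is estimated at only 36% to 38% of this trial, the protocol itself calls the RTOG 85-31 subset less favourable, and the cited later trial is used only for the control rate.

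Two further inferences go too far:

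- That the 75% in 13.8.2 was miscalculated. It was stated for the 1997 schedule and reproduces there.
- That 716 deaths leave disease-specific survival clearly short of its 90% power. Shares of 29% to one third give about 208 to 239 events and 82% to 87% power, but section 11.3.11 also counts treatment-related deaths and some deaths of unknown cause. If all 17 unknown deaths in the 13.6 table counted, the share would be 93/258 = 36%, about 258 events, and power would be close to 90%.

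It is also fair that sections 13.6 and 13.8.2 already warn about overall survival. Those warnings predate the change of primary endpoint, and section 13.4.1 does not take them up.

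**Conclusion.** The concern holds as an unreconciled effect assumption, not as an arithmetic error. The 90% at 716 deaths is correct for 21.6%, but that effect is underived and larger than the retained text expects. At the protocol's own 11%, power is about 34%; at 16.7%, the most its expectation allows at the average ratio, it is about 69%. The 75% in section 13.8.2 does not describe the 716-death analysis, and section 13.7 contradicts both section 13.8.2 and itself.

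The power figures rest on proportional hazards and 1:1 allocation. The 65% to 74% also assumes no effect on other causes of death and a prostate-cancer share between 29% and one third. The 74% check in step 4 uses the 2008 control hazard, because the 1997 hazard curves are not shown.

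A reader might conclude that a non-significant overall survival result can never exclude the 11% benefit. That is not so in general: the standard error of ln HR is about 2/√716 = 0.075, so an observed HR above about 0.89 × exp(1.96 × 0.075) = 1.03 has a 95% interval that excludes 0.89. Between 0.864 and 1.03, the result would be non-significant and still compatible with 0.89.

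**What to change.** - **13.4.1:** justify the 7-point gain against section 13.8.1, and state beside the 90% that power at 716 deaths is about 69% for a 16.7% reduction and about 34% for 11%. Add that a non-significant overall survival result will be interpreted from its confidence interval relative to HR 0.89.
- **13.8.2:** label the 75% as belonging to the 1997 design, and add that at 716 deaths it is about 69%.
- **13.7:** state that 1980 patients were sized on disease-specific survival and that the 716 deaths were set for overall survival. Delete the sentence that makes all-cause survival secondary.

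The cost is wording only. No patients or deaths are added and no test changes; the power on the page becomes less favourable.

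### The final analysis is set at 716 deaths in 13.4.1 but eight years after accrual in 13.8.2, and the only power stated for disease-specific survival (90%) does not apply at 716 deaths

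*Protocol*

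**What the plan says.** All of the following stands in the current protocol text.

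- **Section 13.4.1** (within 13.4, last dated 7/14/08) makes overall survival (OS) the basis of the final analysis: "716 deaths are required to detect a 21.6% relative reduction in the yearly death rate with 90% statistical power", one-sided "at the 0.025 significance level", and "A final analysis will be performed when 716 deaths occur". Sections 13.2.1 and 13.7, both dated 7/14/08, also name OS as primary.
- **Section 13.8.2** (13.8 is dated 7/1/97 only) treats DSS as primary: "we will use a two-sided log-rank test to detect the treatment effect of 33% reduction in hazard of death from prostate cancer", at two-sided 0.05 and 90% power, with 1779 evaluable patients "accrued uniformly over five years and followed for additional eight years before the final analysis". The total becomes 1980 after allowing for 10% unevaluable.
- **Section 13.6** (7/1/97), below the cause-of-death table, describes the 1997 change to "disease specific survival as the primary endpoint with a median of 10 years follow-up".
- **Section 13.3** opens by pointing to the sample size of 1980, but retains the final-analysis timing of the 670-patient design: three years of accrual and three more of follow-up.
- **Section 13.4** keeps 261 (in one paragraph 260) prostate-cancer deaths as the required maximum and describes DSS as the primary endpoint of the interim analyses.
- **Section 13.4.2** tests DSS as a secondary endpoint at 0.025 and gives it no event count or date.
- **Section 13.7** says that the sample size is calculated on OS, yet the only derivation of 1980 is the DSS one in 13.8.2.

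**The concern.** Two rules now define the final analysis: an all-cause death count and a calendar point. If they fall at different times, the number of DSS events differs too, and so does DSS power. The only DSS power in the protocol belongs to the calendar design with about 261 prostate-cancer deaths. DSS was the primary endpoint from 1997 until the 2008 change and is listed first among the secondary endpoints. If it is analysed at 716 deaths and shows no difference, a reader who turns to 13.8.2 will judge that result against 90% power, when the cut-off may deliver clearly less.

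**Working it through.** **1. The stated figures reproduce.**

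OS: −ln(0.60)/8 = 0.0639 and −ln(0.67)/8 = 0.0501, a hazard ratio of 0.784. At one-sided 0.025 and 90% power, Schoenfeld's formula, 4(1.960 + 1.282)²/(ln 0.784)², gives 710 deaths and Freedman's gives 717. With 716 deaths, power is 90.2%.

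DSS: power = Φ(|ln 0.67|·√D/2 − 1.96). With D = 261, this is Φ(0.4005 × 16.16/2 − 1.96) = Φ(1.275) = 89.9%.

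**2. When 716 deaths occur.** Inputs are the 13.4.1 hazards (exponential), equal arms and the uniform five-year accrual of 13.8.2 (A = 5). Expected deaths at time T from the start of accrual are the sum over arms of (N/2)·[1 − (e^(−λ(T−A)) − e^(−λT))/(λA)]. The control hazard is 0.0639. The Arm 1 hazard is either 0.0501 (the 13.4.1 effect) or 0.0639 × 0.89 = 0.0569 (the 11% all-cause reduction in 13.8.1).

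| N | Arm 1 hazard | 716 deaths, years after closure | Deaths expected at 8 years |
|---|---|---|---|
| 1980 | 0.0501 | 5.5 | 885 |
| 1980 | 0.0569 | 5.0 | 925 |
| 1779 | 0.0501 | 6.6 | 795 |
| 1779 | 0.0569 | 6.1 | 831 |

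The count is therefore reached 1.4 to 3.0 years before the eight-year point. Section 13.8.2 agrees indirectly: its 75% power for a 16.7% all-cause reduction needs about 832 deaths, so that design expected well over 716.

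**3. Eight years and a median of 10 years.** Five years of uniform accrual plus eight years gives a median potential follow-up of 13 − 2.5 = 10.5 years. Sections 13.6 and 13.8.2 describe one design.

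**4. DSS events among 716 deaths.** Let s be the control-arm share of deaths due to prostate cancer. With a DSS hazard ratio of 0.67 and other-cause mortality unchanged, the share over both arms is 1.67s/[1.67s + 2(1 − s)]. This ignores differential depletion of the arms. DSS events are 716 times that share, and power follows from the formula in step 1.

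| s | Source | Share, both arms | DSS events | Power |
|---|---|---|---|---|
| 26.3% | 49/186, RTOG 77-06, Gleason 2-6 | 23.0% | 165 | 73% |
| 29.5% | 76/258, RTOG 77-06, combined | 25.9% | 185 | 78% |
| 33.3% | 11/33, the translation in 13.8.1 | 29.5% | 211 | 83% |
| 36.0% | (76 + 17)/258, all unknown causes counted | 32.0% | 229 | 86% |

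The two middle rows supply 71% to 81% of 261 events.

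**5. Break-even.** To have 261 DSS events among 716 deaths, the share over both arms must be r = 261/716 = 36.5%. Then s = 2r/(1.67 + 0.33r) = 0.729/1.790 = 40.7%. That is about the RTOG 77-06 share for Gleason 7-10 alone (25/62 = 40.3%), whereas 13.8.1 expects only 36% to 38% of this trial's patients to be in that group.

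**The case against.** The strongest reply is that the dates already settle the matter. Section 13.8 is dated 1997, the OS sections 2008, and 13.4.1 is explicitly the primary analysis. A careful reader would take 716 deaths as the OS trigger and the rest as text left from an older design. For OS, this largely stands. It does not settle DSS: 13.4.2 sets no cut-off, and 13.4, which also carries the 2008 date, still calls for 260 or 261 prostate-cancer deaths.

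A reader might infer that three different stopping rules compete. The documents do not support that of 13.4.1, 13.6 and 13.8.2. The median in 13.6 matches the eight-year design and appears in an account of the 1997 amendment. The timing that does differ from both rules is the three additional years in 13.3.

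A reader might also infer that the protocol promises 90% DSS power at 716 deaths and has miscalculated it. It does neither. The 90% is stated for DSS as primary at about 261 events, and there it is correct.

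Finally, the loss of power depends on the share assumed. The DSS definition in 11.3.11 counts treatment deaths and some deaths of unknown cause, which raises the share. Section 13.8.1 also describes all-cause hazards 3 to 4 times the prostate-cancer hazard for Gleason 2-6 and about 2 times for Gleason 7-10. With 36% of patients in the latter group, that gives shares of 0.64/4 + 0.36/2 = 34% to 0.64/3 + 0.36/2 = 39%, or 215 to 251 events and 84% to 89% power. This stands: no single figure should be presented as the DSS power. These readings narrow the gap, but all remain below 261 events.

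**Conclusion.** The point holds as a conflict between two final-analysis rules, with an unretired third timing in 13.3, and as a DSS power statement tied to a design that no longer governs. It is not an arithmetic error, and it does not touch the power of the OS analysis.

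If DSS is analysed at 716 deaths, the protocol's combined RTOG 77-06 share and its 33%-to-11% translation give about 185 to 211 events and 78% to 83% power for a 33% reduction. Across shares of 26% to 36% the range is about 73% to 86%. These figures assume a DSS hazard ratio of 0.67, no treatment effect on other-cause death, and a test at two-sided 0.05 (equivalently one-sided 0.025). The timing assumes exponential survival at the 13.4.1 hazards and uniform five-year accrual. If the sponsor instead waits for about 261 prostate-cancer deaths, the 90% is valid, but nothing in 13.4.2 says so.

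**What to change.** 1. State in 13.4.1 that 716 deaths is the single trigger for the final OS analysis.
2. Mark as superseded the timing and primary-endpoint statements in 13.3, 13.6 and 13.8.2, and the wording in 13.4 that treats DSS as primary.
3. For DSS, choose one course and write it into 13.4.2. Either analyse DSS at 716 deaths and give the expected events and power with the assumed share and its range (for example, 185 to 211 events and 78% to 83% at control shares of 29.5% to 33.3%, and 73% to 86% at 26% to 36%). Or fix the definitive DSS analysis separately at about 261 prostate-cancer deaths, using the lifelong follow-up already in 11.2.3.

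The cost is wording. The first course prints a less favourable power figure; the second means a later DSS analysis. Neither needs more patients.

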## **10.0 PATHOLOGY (4/1/95, 7/1/97, 7/14/08)**

**10.1** Central pathology review of the diagnostic and of the 2-year biopsies are planned for this study. Central reviews of previous prostate studies have demonstrated a 34% discrepancy in histological grading.

**10.2** Hematoxylin and eosin(*H & E*) stained slides and a representative tissue block of all pathologic material, the pathology report and a pathology submission form will be submitted to:

Mailing Address: For Non-frozen Specimens Only

RTOG Biospecimen Resource  
University of California San Francisco  
[name]  
[name]  
[name]

Courier Address (FedEx, DHL, etc.): For Frozen Specimens

RTOG Biospecimen Resource  
University of California San Francisco  
[name]  
[name]

Questions: [name]/[contact]; [contact]

**10.2.1** H& E stained slides will be retained until completion of the analysis of the study. Slides will be returned if specifically requested at that time.

**10.2.2** Blocks will be retained for the special studies outlined below. Slides prepared from the blocks will also be retained.

- 10.2.3** If blocks will not be released, submission of 10 unstained sections mounted on sialinized (*or other "sticky slides"*) may be substituted.
- 10.3** All pretreatment biopsies will be assessed for the presence of tumor and graded according to Gleason (*see Appendix V*).
- 10.4** DNA content and proliferation rate will be assessed in all cases by image analysis (*Feulgen staining*) and immunocytochemistry (*MIB-1 antibody*).
- 10.5** Pretreatment biopsies of patients randomized to receive hormone ablation will be evaluated for expression of the bcl-2 proto-oncogene by immunohistochemistry. Overexpression of bcl-2 has been found to correlate with hormone resistance. In this study, the potential value of bcl-2 as a predictor of hormone resistance will be studied.
- 10.6** Post-treatment biopsies will be assessed for the presence of persistent tumor.
- 10.6.1** All positive biopsies will be histologically graded according Gleason and the degree of therapy effect in the tumor cells will be graded according to Dhom and Degro.
- 10.6.2** In cases where there is difficulty in diagnosis, immunohistochemical staining for high molecular weight cytokeratin will be performed to aid in the distinction of atypical benign glands from carcinoma.

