## **13.0 Statistical Considerations**

### **13.1 Study Design**

The objectives of the trial are described in Section 2.0. They can be met by a randomized comparison of two groups testing neoadjuvant total androgen suppression (*TAS*) before/during RT versus RT alone.

Treatment allocation will be done by randomized permuted blocks within strata to balance for prognostic factors. Stratification will be done by PSA (< 4, 4-20) and differentiation (*well*, *moderate*, *poor*), and nodal status (*N0*, *NX*).

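### Randomization is stratified by PSA, differentiation and nodal status, but the log-rank tests in 13.4.1 and 13.4.2 are not stated to be stratified: a small loss of power that can be recovered almost for free (minor)

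*Protocol*

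**What the plan says.** Section 13.1 states: "Treatment allocation will be done by randomized permuted blocks within strata to balance for prognostic factors". The factors are PSA (<4, 4-20), differentiation (three levels) and nodal status (N0, NX), which makes 2 x 3 x 2 = 12 cells.

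Section 13.4.1 sets the primary analysis of overall survival: "This hypothesis will be tested using a log-rank test statistic at a significance level" of 0.025. Nothing there says the test is stratified. Section 13.4.2 tests disease-free survival and the other secondary time-to-event endpoints by log-rank, again with no mention of strata.

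The strata do appear in the supporting regression. Section 13.4.1 asks for unadjusted and adjusted Cox hazard ratios: "At least the treatment arm, the stratification variables (PSA, grade, and nodal status), age, and race (as appropriate) will be adjusted for". Section 13.4.2 has a matching list for its Cox and Fine-Gray models. Gleason score is in neither list.

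On Gleason score, 13.6 says: "We also acknowledge that Gleason score is a significant risk factor and must be included in the design". Section 13.4 names it for exploratory Cox modelling. Under 4.3 grade is mandatory, while Gleason score is asked for where it can be had.

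**The concern.** The design treats three factors as prognostic enough to balance on, but the test that decides the trial is not said to condition on them. With a log-rank test, heterogeneity between strata that is left out of the analysis attenuates the marginal hazard ratio relative to the ratio within strata. The loss comes from that attenuation, not from a larger standard error. The 716-death target assumes one exponential hazard per arm, so it makes no allowance for it. What is at stake is a small part of the stated 90% power, on the primary endpoint and likewise on the secondary ones.

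**Working it through.** **1. The plan's own figure.** Inputs from 13.4.1: 8-year survival of 60% on Arm 2 and 67% on Arm 1, one-sided 0.025, 90% power.

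- Hazards: -ln(0.60)/8 = 0.0639 and -ln(0.67)/8 = 0.0501 per year. Ratio 0.784, a 21.6% reduction.
- Schoenfeld: 4 x (1.960 + 1.282)² / (ln 0.784)² = 710 deaths.
- Freedman: (1.960 + 1.282)² x (1.784/0.216)² = 717 deaths.
- Power at 716 deaths (Schoenfeld): 90.3%.

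The plan says "716 deaths are required to detect a 21.6% relative reduction in the yearly death rate with 90% statistical power", and this reproduces. Both formulas are for an unstratified test in a homogeneous population.

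**2. Effect of stratifying.** The protocol gives neither the share of patients in each stratum nor the all-cause hazard ratios between strata. I assumed 10% with PSA <4, grade 25/55/20% and 10% N0, and varied the stratum effects. Simulation: 1,980 patients, 5-year uniform accrual, blocks of 4 within the 12 cells, analysis at 716 deaths, control 8-year survival calibrated to 60%, hazard ratio 0.784 within strata, 8,000 trials per row. Both tests were run on the same data.

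| Assumed hazard ratios (PSA; per grade step; nodal) | Unstratified | Stratified | Information ratio |
|---|---|---|---|
| none (1; 1; 1) | 89.8% | 89.7% | 0.996 |
| moderate (1.2; 1.3; 1.1) | 89.6% | 89.9% | 1.011 |
| strong (1.5; 1.6; 1.2) | 89.2% | 89.9% | 1.047 |
| very strong (2.0; 2.0; 1.3) | 88.0% | 90.0% | 1.112 |

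The information ratio is the squared ratio of mean test statistics, for example (3.2584/3.1846)² = 1.047. Applied to 716 deaths, the gains equal about 0.011 x 716 = 8, 0.047 x 716 = 34 and 0.112 x 716 = 80 deaths. In the first row the cost is about 0.004 x 716 = 3 deaths. The Monte Carlo standard error of one power figure is √(0.9 x 0.1/8000) = 0.3 points.

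**3. Type I error.** With 2,000 null trials per scenario (6.5-year accrual), the unstratified test rejected in 2.3% to 2.9% against a nominal 2.5%. The standard error is √(0.025 x 0.975/2000) = 0.35 points, so the results are consistent with nominal.

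**4. Sparse cells.** Under the assumed shares the smallest cell (PSA <4, poorly differentiated, N0) holds 1,980 x 0.10 x 0.20 x 0.10 = about 4 patients. The simulation did not pool cells, so the first row already shows what sparse cells cost.

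**5. How prognostic Gleason score is for all-cause death.** The ratios in 13.8.1 (3-4 for Gleason 2-6, about 2 for 7-10) compare all-cause with prostate-cancer hazard within each group. They are not the effect of Gleason score on survival. If other-cause mortality is equal in the two groups, the implied all-cause hazard ratio runs from (1 - 1/3)/(1 - 1/2) = 1.33 to (1 - 1/4)/(1 - 1/2) = 1.5. The RTOG 77-06 death shares in 13.6 (26% and 40% from prostate cancer) give 0.74/0.60 = 1.23. Stratifying on Gleason score alone, with 37% in the high group (13.8.1 gives 36% and later 38%), moved power from 89.8% to 89.8% at a hazard ratio of 1.2 and from 89.5% to 90.0% at 1.5. At 2.0, outside the implied range, it moved from 88.8% to 89.8%.

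**The case against.** The case against has force. An unstratified log-rank test after stratified allocation is a standard and valid choice. The adjusted model already carries all three factors and meets the attenuation of the estimate. The simulated gain is at most 0.7 points unless the strata are very strongly prognostic. With 12 cells, some could be nearly empty. Whether a log-rank test is stratified is also a detail that a statistical analysis plan often settles, and none is shown here.

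Most of that stands, and it is why the point is minor. It does not remove it. The protocol itself fixes the test and the minimum covariate list, and the hypothesis is decided by the log-rank test, not by the adjusted model. If an analysis plan does stratify, 13.4.1 and 13.4.2 should say the same.

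A reader might also infer four stronger things that the protocol does not support:

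- *That the strata are ignored throughout.* They are in the adjusted models of 13.4.1 and 13.4.2.
- *That the protocol requires Gleason score as a covariate.* Section 13.6 speaks of the design and dates from the 1997 revision, when disease-specific survival was primary. Section 13.8 acts on it, with Gleason-specific control hazards and separate power for Gleason 7-10. The covariate lists are also minimum lists.
- *That the test's error rate is conservative.* The simulated null error is around nominal.
- *That Gleason 7-10 doubles mortality, so that leaving it out costs real power.* The protocol's figures point to roughly 1.2 to 1.5. Nor does the protocol rank Gleason score as the strongest factor.

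**Conclusion.** The concern holds as a minor one. The confirmatory log-rank tests are not stated to use the strata that governed randomization. The cost is about 0 to 0.7 points of power for stratum effects from none to strong, and about 2 points only if they are very strong. The tests remain valid, and 716 deaths remains the right count for the stated assumptions.

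The size rests on assumed stratum shares and effects, and on taking 0.784 as the hazard ratio within strata. If the 60% and 67% survival rates are instead taken as holding for the arms as a whole, the gain would appear more as power above 90% than as a shortfall below it.

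The absence of Gleason score from the named covariates is neither an error nor a contradiction. Naming it would be a reasonable optional addition.

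**What to change.** In 13.4.1 and 13.4.2, state that the log-rank tests are stratified by PSA (<4, 4-20), differentiation and nodal status as used at randomization. Fix in advance a rule for pooling cells with few events, and report the unstratified test as a sensitivity analysis. If the unstratified test is preferred as primary, give the reason.

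Optionally, name Gleason score (2-6 vs 7-10) in the adjusted models. State whether the central or the institutional reading is used and how missing scores are handled. The source matters because, according to 10.1, central reviews of earlier prostate studies "have demonstrated a 34% discrepancy in histological grading".

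The cost is analysis wording only. The event target and data collection are unchanged, and the only statistical downside is a negligible loss if some cells are sparse or the strata turn out not to be prognostic.
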